## Abstract

**Background::**

Diabetic macular edema (DME) can cause severe vision impairments for patients with diabetes. Recently, Conbercept has shown efficacy on DME with 3-monthly loading dose injection and pro re nata (PRN, 3+PRN) thereafter in retrospectivetrials. Furthermore, there are some other approaches have been recommended such as 2mg bimonthly (2q8) after 5 initial doses, or Conbercept 0.5mg treat-and-extend, however, some patients still have recurrence of the disease after treatment. Therefore, in order to identify more efficacy and safety approach on Conbercept inpatients with DME, a randomized controlled trial will be performed with 6-monthly loading dose injection and PRN (6+PRN) compared with 3+PRN treatments.

**Methods::**

This study is a multicenter, randomized control trial of Conbecept treating DME in China. Patients with type 2 diabetes suffered from DEM who already planned to receive Conbercept treatment will be recruited. All subjects will be randomized divided into either a study agent treatment group (6+PRN) or a control group (3+PRN), and observes the subjects for 48 weeks after initiation of treatment.

**Results::**

This study will provide a new powerful evidence of the efficacy and safety of Conbecept treating DME.

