Previously, a retrospective study evaluated the therapeutic efficacy of conbercept for treatment of DME patients received one initial intravitreal injection of Conbercept (IVC) followed by retreatment based on best-corrected visual acuity (BCVA) loss or central subfield thickness (CST) increase and found that the mean improvement in BCVA was significantly greater in the Conbercept-treated groups than that of the corresponding untreated controls at 12 months. In addition, the mean CST was significantly reduced in the Conbercept treatment groups as compared to that of the corresponding untreated controls. Furthermore, another retrospective clinical study showed that DME patients initially treated with 1 to 3 consecutive monthly IVC injections could be effective for visual and anatomic improvements.^[9,10]^ However, there is no report from randomized controlled trial based evidence on IVC for DME. In addition, there are some regimens of intravitreal anti-vascular endothelial growth factor (VEGF) treatment on DME such as Treat-and-extend or pro re nata (PRN; “as needed”) regimens have been found to reduce the injection burden on patients.^[11]^ In clinic, patients with DME often require multiple treatments, and some patients have poor or even no response to the drugs, thus, there is a need to conduct a randomized controlled trial study to identify a more effectiveness approach on IVC for DME.

This aim of this study was to assess the safety and efficacy of 6 + PRN therapy with anti-VEGF agent, Conbercept in patients with T2DM and DME, and to compare the traditional 3+ PRN regimen.

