### Randomization

2.6

All participants will be randomised 1:1 using computer-generated randomization, with sequentially numbered, to receive either 3 + PRN or 6 + PRN treatment. All participants are single-masked of the allocation and regimen after randomization. Randomization is advised to be conducted on the day of IVC treatment.

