### Interventions

2.7

All patients in 3 + PRN group will receive a minimum of 3 initial monthly IVC (0.5 mg) injection, PRN dosing thereafter BCVA and CST stabilization criteria-driven PRN treatment while 6 + PRN group will receive a minimum of 6 initial monthly IVC (0.5 mg) injection, PRN dosing thereafter BCVA and CST stabilization criteria-driven PRN treatment.

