### Statistical analysis

2.11

SPSS statistical software (IBM Statistics, v. 22.0; IBM Corp, Armonk, NY) will be used to conduct analysis. Quantitative data, BCVA, is represented by median (quartile), and other data is represented by mean and SD. The comparison of clinical features between groups was performed using the *t* test. Changes in BCVA before and after treatment were tested using Wilcoxon–Matt–Whitney test. The change of CST and indicators of retinal blood flow from baseline were analyzed by paired *t* test. The comparison of different follow-up time indicators was performed by repeated measurement data analysis of variance. Statistical significance will be based on 2-sided tests, with *P* value less than .05 taken as the criterion for statisticalsignificance.

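### Every participant receives Conbercept, so the trial can compare only 6+PRN with 3+PRN, yet the abstract claims evidence on the drug itself and section 2.11 words its outcome tests as before/after tests

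*Protocol article*

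**What the plan says.** **The claim.** The abstract (Results) promises: "This study will provide a new powerful evidence of the efficacy and safety of Conbecept treating DME". No comparator is named. The Introduction gives as part of the rationale that "there is no report from randomized controlled trial based evidence on IVC for DME". It then states an aim whose first half is non-comparative, to "assess the safety and efficacy of 6 + PRN therapy with anti-VEGF agent, Conbercept in patients with T2DM and DME", and whose second half is a comparison with the 3+PRN regimen.

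**The design.** The abstract (Methods) recruits patients "who already planned to receive Conbercept treatment will be recruited" and allocates them to "either a study agent treatment group (6+PRN) or a control group (3+PRN"). Section 2.6 randomises 1:1 "to receive either 3 + PRN or 6 + PRN treatment". Under section 2.7, "All patients in 3 + PRN group will receive a minimum of 3 initial monthly IVC (0.5 mg) injection", and the other arm receives at least six at the same dose; both then continue PRN. No arm is untreated, sham-treated or given another therapy.

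**The analysis.** Section 2.11 says: "The change of CST and indicators of retinal blood flow from baseline were analyzed by paired" *t* test. The BCVA test is worded as comparing values before and after treatment, and the test named appears to be Wilcoxon-Mann-Whitney. A between-group *t* test is stated for clinical features, and a repeated-measures analysis of variance for the follow-up times.

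**The concern.** The sentence in the abstract and the randomised contrast answer different questions. One is whether Conbercept works and is safe in DME. The other is whether six initial injections do better than, or no worse than, three. Only the second is protected by randomisation here.

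On its own the abstract sentence would be a matter of editing. It matters because section 2.11 gives it a route into the results. The tests tied by name to CST and retinal blood flow are within-patient, and the BCVA test is worded the same way. If the arms turn out similar and both change from baseline, the P values nearest to hand would be before/after ones. They look like support for the drug-level claim, and they leave the schedule question unanswered. The gap in randomised evidence named in the Introduction could then appear filled for drug efficacy when it is not.

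**Working it through.** **1. What randomisation identifies.** Let each arm's mean change from baseline be the sum of a drug effect under its schedule and a non-drug change (natural course, test practice, changes in diabetes care):

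- 6+PRN: D6 + N
- 3+PRN: D3 + N

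Randomisation makes N the same in expectation in both arms. The between-arm difference is (D6 + N) - (D3 + N) = D6 - D3, so N cancels. A within-arm test examines D6 + N or D3 + N, and N stays in. Nothing in the design estimates D6 or D3 alone, because no arm has D = 0. The same holds for the drug's side effects: the arms can be compared with each other, but not with patients who do not receive the drug.

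**2. Which question each part of the protocol asks or answers.**

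| Place | Question |
|---|---|
| Abstract, Background | 6+PRN against 3+PRN |
| Abstract, Results | The drug, no comparator |
| Abstract, Discussion | Whether more treatments are more effective |
| Introduction, rationale | Lack of randomised evidence on the drug, leading to a need for a more effective approach |
| Introduction, aim | 6+PRN alone, then against 3+PRN |
| Section 2.1 | 6+PRN against 3+PRN |
| Section 2.10 | Non-inferiority, and superiority, of 6+PRN |
| Section 2.11, CST and blood flow | Change from baseline, paired |
| Section 2.11, BCVA | Worded before/after; the named test is normally for independent samples |
| Section 2.11, clinical features | Between groups |

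The aims and the sample-size objective are mostly comparative. The abstract's Results sentence and the CST and blood-flow tests do not match them, and the BCVA test is unclear.

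**3. How small a change a within-arm test calls significant.** The claim depends on no figure in the plan, so there is none to reproduce. As a scale only, take the 50 per group of section 2.10 and the two-sided 0.05 level of section 2.11.

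- Paired *t* test in one arm: significant when the mean change exceeds t(0.975, 49)/√50 = 2.010/7.071 = 0.28 SD of the change. With 60 per group: 2.001/7.746 = 0.26 SD.
- Between-arm *t* test of change, assuming equal SDs: significant when the difference exceeds t(0.975, 98) × √(2/50) = 1.984 × 0.200 = 0.40 SD.

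Now suppose the drug had no effect and the non-drug change were d SDs. The documents give no value for d, so a range is shown. The chance that one arm's paired *t* test is significant (noncentral *t*, non-centrality d√n) is:

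| d | n = 50 | n = 60 |
|---|---|---|
| 0.2 | 0.28 | 0.33 |
| 0.3 | 0.55 | 0.63 |
| 0.4 | 0.79 | 0.86 |
| 0.5 | 0.93 | 0.97 |

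The between-arm test keeps its 5% error rate for every d, because N cancels.

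**The case against.** **The comparative aim is stated repeatedly.** The abstract's Background and Discussion and sections 2.1 and 2.10 all ask about one schedule against the other, and the Introduction's aim ends with that comparison. The quoted sentence fills the Results slot of a protocol abstract and sets no decision rule. This stands: the design can address its schedule question, and the fault lies in the stated conclusion and the tests.

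**The BCVA test may be comparative.** Wilcoxon-Mann-Whitney is normally an independent-samples test, so it could be meant to compare BCVA change between arms. This also stands. A reader might infer that the primary outcome will be tested only within arms; the text does not settle that. The wording is unclear and has to be fixed either way. The repeated-measures analysis might include a group term, but the section does not say so.

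**Stronger readings that the document does not support.**

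- A reader might infer that the plan will declare Conbercept effective from before/after P values. Section 2.11 attaches no efficacy conclusion to any of them.
- A reader might infer that no result could bear on efficacy. Clear superiority of 6+PRN would be indirect randomised evidence that the extra injections have an effect, though not an estimate of the drug's effect.
- A reader might infer that entry selects for regression to the mean. The criteria in section 2.3 do not clearly do so: acuity has only a lower limit, and CST on either side of 300 microns can qualify. The argument above needs only that non-drug change is possible.
- A reader might fault the article for giving no precision for side-effect rates. That is ordinary content of an analysis plan that is not shown.

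**The paired tests are not an omission.** The full analysis plan may add between-arm analyses, but the paired *t* test for CST and blood flow is what this document states.

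**Conclusion.** The point holds as a mismatch between the claim, the stated tests and the randomised contrast. All participants receive Conbercept, so the trial can support a conclusion only about 6+PRN relative to 3+PRN. The abstract's claim about the drug's efficacy and safety goes beyond that. The paired tests in section 2.11 do not answer the randomised question, and the BCVA test is ambiguous.

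The size is inferential: no figure in the plan changes. The 0.28 SD threshold rests on 50 analysed patients per arm, a two-sided 0.05 level and a paired *t* test. That test is assigned to CST and blood flow, so the threshold should not be read across to BCVA. The probabilities in the table depend on an assumed non-drug change, which the documents do not give. The conclusion does not depend on them: a within-arm P value cannot be attributed to the drug, however large or small that change is.

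**What to change.** - **Section 2.11.** Make the between-arm comparison of change from baseline at weeks 24 and 48 the basis for inference on BCVA, CST and OCTA metrics. Name the BCVA test correctly and say that it compares the arms. Report within-arm changes descriptively, as an estimate with 95% CI and no efficacy conclusion.
- **Abstract, Results.** State the expected conclusion as evidence on 6+PRN relative to 3+PRN among patients who all receive Conbercept.
- **Introduction.** Word the rationale and aim the same way, so that the trial is not presented as filling the gap in randomised evidence on the drug itself.

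The first change matters most, since it decides what the trial's P values refer to; rewording the abstract alone would be close to editorial. The cost is a few sentences and a narrower claim. No arm, patient, visit or measurement is added.

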**Discussion::**

This RTC study will determine whether multiple treatments of Conbercept provide better effectiveness in patients with DME.

**Trial registration number::**

ChiCTR2000032728

## Introduction

1

Diabetic retinopathy (DR) was the most common cause of bilateral blindness in working-age population in the world.^[1–3]^ Diabetic macular edema (DME) is one of the important causes of visual impairments caused by DR. A recent systematic review and meta-analysis showed that DME were prevalent in 3.7% (95% CI 2.2–6.2%). The pooled mean annual incidence of DME in persons with type 2 diabetes was 0.4% (95% CI 0.5–1.4%). It is estimated that persons with diabetes affected by DR and DME in Europe will be up to 8.6 million in 2050, of whom 30% require treatment.^[4]^ Vascular endothelial growth factor (VEGF) is an important factor in the destruction of the blood-retinal barrier, which can lead to blood vessel leakage and macular edema.^[5]^ The level of VEGF in the eyes of DME patients increases, so it is proposed that the use of anti-VEGF (anti-VEGF) drugs may control the process of vision loss or even loss in DME patients.

Conbercept is a new fusion protein, which contains Fc segments of human VEGF receptor 1, VEGF receptor 2, and human IgG-1. It can be combined with VEGF-A, VEGF-B, VEGF-C, and placental growth factor (PlGF).^[6–8]^ In May 2019, Conbercept had been approved to use for the treatment of the DME by China Food and Drug Administration.

Previously, a retrospective study evaluated the therapeutic efficacy of conbercept for treatment of DME patients received one initial intravitreal injection of Conbercept (IVC) followed by retreatment based on best-corrected visual acuity (BCVA) loss or central subfield thickness (CST) increase and found that the mean improvement in BCVA was significantly greater in the Conbercept-treated groups than that of the corresponding untreated controls at 12 months. In addition, the mean CST was significantly reduced in the Conbercept treatment groups as compared to that of the corresponding untreated controls. Furthermore, another retrospective clinical study showed that DME patients initially treated with 1 to 3 consecutive monthly IVC injections could be effective for visual and anatomic improvements.^[9,10]^ However, there is no report from randomized controlled trial based evidence on IVC for DME. In addition, there are some regimens of intravitreal anti-vascular endothelial growth factor (VEGF) treatment on DME such as Treat-and-extend or pro re nata (PRN; “as needed”) regimens have been found to reduce the injection burden on patients.^[11]^ In clinic, patients with DME often require multiple treatments, and some patients have poor or even no response to the drugs, thus, there is a need to conduct a randomized controlled trial study to identify a more effectiveness approach on IVC for DME.

This aim of this study was to assess the safety and efficacy of 6 + PRN therapy with anti-VEGF agent, Conbercept in patients with T2DM and DME, and to compare the traditional 3+ PRN regimen.

## Subjects and methods

2

Ethical approval for this study was granted by the Office for Research Ethics Committees of Hohhot Chao Ju Eye Hospital ([2020] KY0501). This study protocol was registered at the Chinese clinical trial registry (Chictr.org.), ChiCTR200032728.

### Study design and setting

2.1

This is a multicentre, randomised, equivalence, single-masked clinical trial set within specialized Eye Hospitals involving Hohhot Chao Ju Eye Hospital, Chifeng Chao Ju Eye Hospital, Baotou Chao Ju Eye Hospital, Datong Chao Ju Eye Hospital, Jining Chao Ju Eye Hospital and Bayannur Disabled Persons’ Federation Eye Hospital in China. It aims to evaluate the clinical effectiveness and safety of 6 + PRN IVC, when compared with 3 + PRN IVC, for the treatment of patients with DME.

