### Sample size

2.10

This study is powered to demonstrate non-inferiority of 6 + PRN with respect to the effective rate (at 48 weeks). The trial will have sufficient statistical power to determine superiority of 6 + PRN treatment over the 3 + PRN. According to our clinical application, we initially expect the effective rate of IVC for DME to be around 75%. After calculation, 50 cases are required for each group. Considering the shedding rate of 20%, 60 cases are required for each group, and a total of 120 cases for the 2 groups.

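### The trial is labelled equivalence, sized for non-inferiority and also claimed to show superiority, with only difference tests and no margin: as printed, a non-significant result supports neither equivalence nor non-inferiority

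*Protocol article*

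**What the plan says.** The protocol article describes the hypothesis differently in different places.

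- **Section 2.1, Study design and setting:** "This is a multicentre, randomised, equivalence, single-masked clinical trial set within specialized Eye Hospitals". The aim given there is neutral: to evaluate 6+PRN against 3+PRN.
- **Section 2.10, Sample size:** "This study is powered to demonstrate non-inferiority of 6 + PRN with respect to the effective rate (at 48 weeks". The next sentence reads: "The trial will have sufficient statistical power to determine superiority of 6 + PRN treatment over the 3 + PRN".
- **Abstract, Discussion:** "This RTC study will determine whether multiple treatments of Conbercept provide better effectiveness in patients with DME". The Abstract's Background and the rationale in the Introduction also look for a more effective approach, although the Introduction's closing aim sentence is neutral.
- **Section 2.11, Statistical analysis:** the methods are a t test for clinical features between groups, a rank test for BCVA before and after treatment, paired t tests for CST and retinal blood flow, and repeated-measures analysis of variance. The decision criterion begins: "Statistical significance will be based on 2-sided tests", with P below .05.

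The sample size rests on one rate, "we initially expect the effective rate of IVC for DME to be around 75" per cent, followed directly by "After calculation, 50 cases are required for each group". The article gives no margin, no separate rate for each arm, no numerical power and no confidence-interval rule.

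**The concern.** Equivalence, non-inferiority and superiority have different null hypotheses, decision rules and sample sizes. Equivalence needs a confidence interval inside two limits, non-inferiority needs it above one limit, and superiority needs it to exclude zero. The only criterion printed, P<.05 in a test of no difference, serves superiority alone.

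If that test is not significant, nothing in the article says how either of the other two claims could be established. A trial that carries the equivalence label leaves room for a null result to be presented as a finding of equivalence. It also leaves room to settle on the hypothesis once the data are known. In addition, non-inferiority of the regimen with more fixed injections would not answer the Abstract's question of whether it works better.

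**Working it through.** **Inputs.** From section 2.10: effective rate 75%; 50 per group before dropout; 60 per group after 20% dropout. From section 2.11: two-sided 5%. My assumptions: 75% true rate in both arms for equivalence and non-inferiority, one-sided 2.5% or 5%, 80% or 90% power, normal approximation.

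**1. Can the 50 be reproduced?** Not from the stated inputs, because margin, power and a second rate are missing. Several unstated combinations come close:
- non-inferiority, 25-point margin: 48 per group (one-sided 2.5%, 80% power) or 52 (one-sided 5%, 90%);
- equivalence by two one-sided tests, 25-point margin: 52 (one-sided 5%, 80%);
- superiority, 75% against 95%: 49 (two-sided 5%, 80%).

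The figure of 50 therefore does not reveal which hypothesis it was calculated for.

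**2. Non-inferiority margin implied by 50 per group.**
SE = √(2 × 0.75 × 0.25 / 50) = 0.0866. Margin = (z for alpha + z for power) × SE.

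| | 80% power | 90% power |
|---|---|---|
| One-sided 2.5% | 2.802 × 0.0866 = 24.3 points | 28.1 points |
| One-sided 5% | 2.486 × 0.0866 = 21.5 points | 25.3 points |

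At 24 points, a true rate of 75 − 24 = 51% on 6+PRN would sit on the boundary of what counts as non-inferior.

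**3. Power at 50 per group for a given margin** (one-sided 2.5%). Non-inferiority: Φ(margin/SE − 1.96). Equivalence: 2Φ(margin/SE − 1.96) − 1, taken as zero where negative.

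| Margin | Non-inferiority | Equivalence | Non-inferiority n per group for 80% power |
|---|---|---|---|
| 10 points | 21% | about 0% | 295 |
| 15 points | 41% | about 0% | 131 |
| 20 points | 64% | 27% | 74 |
| 25 points | 82% | 65% | 48 |

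With 60 × 0.8 = 48 completers, non-inferiority power for 10, 15 and 20 points is 20%, 40% and 62%, so the choice of 48 or 50 hardly matters.

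**4. Superiority at 50 per group against 75%** (two-sided 5%, pooled variance under the null). For 85%: (0.10 − 1.96 × 0.0800)/0.0794 = −0.72, power 24%. The same formula gives 51% for 90% and 81% for 95%.

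**5. What a non-significant difference test can bear.** If 6+PRN were truly 10 points worse (65% against 75%), the two-sided test would be non-significant in about 81% of trials. The 95% CI half-width at 75% is 1.96 × 0.0866 = 17 points.

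**6. The same point for BCVA.** The article gives no SD. For an assumed 4-letter true difference and 48 per arm, P>.05 would occur in about 32% of trials at SD 8 and 75% at SD 15. This illustrates the range and is not an estimate.

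**The case against.** Four points can be made for the plan.

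- **Testing non-inferiority and then superiority is a recognised fixed sequence that needs no alpha penalty.** This stands. The two sentences in section 2.10 do not contradict each other. The sequence still needs a margin and a decision rule, and it does not explain the equivalence label in section 2.1.
- **Two-sided 5% testing is compatible with non-inferiority.** This also stands. A two-sided 95% CI set against a prespecified margin is a standard non-inferiority analysis. The sidedness is not the fault.
- **The article condenses a fuller protocol, and an analysis plan may hold the margin.** It may. A reader might infer that no valid equivalence or non-inferiority conclusion can ever come from this trial. The article does not support that, because a margin fixed in advance elsewhere could supply the missing rule. It would not remove the conflict between sections 2.1 and 2.10 and the Abstract, which is printed here.
- **The power figures assume equal rates.** They do, because only one rate is given. If a true benefit was assumed, a smaller margin could fit: 85% against 75% with a 10-point margin needs 49 per group (one-sided 5%, 80% power). The article states no such benefit.

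A reader might also infer that the investigators intend to call P>.05 equivalence. No sentence says so. The text fails to rule it out, which is a weaker criticism.

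**Conclusion.** The concern holds in a limited form. The article's statements of the hypothesis do not agree: section 2.1 says equivalence, section 2.10 says non-inferiority plus superiority, and the Abstract and the Introduction's rationale ask whether 6+PRN is better. The printed analysis has no margin or interval rule, so as printed a non-significant result could support neither equivalence nor non-inferiority. A superiority conclusion is not barred by difference tests, but calling the power sufficient is not borne out unless the effect is large.

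On size, 50 per group at 75% in both arms gives 80% non-inferiority power only for a margin of about 24 points (22 at one-sided 5%; 28 and 25 at 90% power). Superiority needs about 95% against 75% to reach 81% power. These figures rest on the article's 75% and on assumed alpha, power and equal rates. The matter needs correcting before analysis because it decides which conclusion the trial may draw.

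**What to change.** State one hypothesis throughout. Superiority of 6+PRN over 3+PRN best fits the question asked in the Abstract and the rationale. In that case:

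1. Delete the equivalence label in section 2.1 and the non-inferiority sentence in section 2.10.
2. Amend section 2.11 so that the BCVA test is the between-arm comparison of change. At present it is a rank test of BCVA before and after treatment, summarised by medians, whereas the primary outcome is a mean change.
3. Report the between-arm difference with its 95% CI at the primary time point or points. Section 2.5.1 names both 24 and 48 weeks; if only one is to be primary, say so openly.
4. State that a non-significant result will not be called equivalence or non-inferiority.
5. In section 2.10, replace the claim of sufficient power with the difference that 50 per group can detect. On the effective rate this is about 75% against 95% at 80% power. For a mean BCVA change it is roughly 2.802 × √(2/50) = 0.56 SD, or about 4.5 letters at an assumed SD of 8 and 8.4 letters at 15.

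If the sponsor prefers to keep non-inferiority, section 2.10 should print and justify the margin, the CI-based rule and the alpha and power behind the 50 per group, and place superiority second in a stated order. The equivalence label should still go.

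The changes are to wording and to the BCVA analysis, and need no new data. The article reports 28 eyes recruited by 6 July 2020, so the amendment should be dated and made without sight of outcomes by arm. Under the superiority route, the sponsor gives up a non-inferiority claim that the printed design does not support, and the stated power becomes less favourable.
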